### Discontinuation of the intervention

Participants may withdraw from the study at any time without penalty or any effect on their routine clinical care. Data collected before withdrawal may be retained for analysis unless the participant requests otherwise, and no further study procedures or data collection will be performed after withdrawal. Where feasible, the study team will attempt to contact participants who withdraw in order to document the reasons for discontinuation.

Participants will discontinue the intervention or be withdrawn from the study under any of the following circumstances: (1) the participant requests to discontinue treatment or withdraw from study participation; (2) a serious adverse event occurs that, in the judgment of the investigators or treating clinician, warrants discontinuation; (3) the treating clinician determines that modification of the treatment plan is clinically indicated because of a change in the participant’s condition; or (4) the participant is unwilling or unable to comply with the treatment protocol or study procedures.

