## Outcomes

### Primary outcomes

The primary outcomes of this pilot trial are feasibility, safety, and preliminary clinical efficacy.

Feasibility will be evaluated using three indicators: recruitment feasibility, intervention adherence, and retention at the 6-month follow-up. Recruitment feasibility will be defined as the number of participants successfully enrolled during the 2-year recruitment period. Intervention adherence will be defined as the proportion of participants who complete all 20 planned treatment sessions. Retention will be defined as the proportion of enrolled participants who complete the 6-month follow-up assessment.

Safety will be evaluated by recording the incidence of adverse events and serious adverse events throughout the treatment and follow-up periods. The type, severity, outcome, and relationship of each adverse event to the intervention will be documented.

Preliminary clinical efficacy will be evaluated using the CDRS-R. CDRS-R total score will be assessed at baseline, at the end of treatment (week 4), and at follow-up weeks 8, 16, and 24. Response will be defined as a reduction of at least 50% in the CDRS-R total score from baseline, and remission will be defined as a CDRS-R total score of 28 or lower [28]. Response and remission will be determined at post-baseline assessments, using the baseline CDRS-R total score as the reference.

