### Exploratory outcomes

Exploratory outcomes will include MRI-derived functional connectivity, cognitive performance, and multimodal neurophysiological and behavioral measures. MRI-derived functional connectivity will be analyzed using seed-based or whole-brain approaches to examine modulation of depression-relevant circuits. Cognitive performance will be assessed using THINC-it [32]. Multimodal exploratory biomarkers will be assessed, including electroencephalography (EEG), eye tracking, functional near-infrared spectroscopy (fNIRS), facial expression features, and acoustic features.

These exploratory measures will be collected according to the assessment schedule at baseline, at the end of treatment, and during follow-up where applicable. They will be used to characterize potential cognitive, neurophysiological, behavioral, and affective changes associated with treatment and are not designated as primary or secondary outcomes. The schedule of outcome assessments is shown in Table 1.

**Table 1 pone.0355676.t001:** Study of efficacy outcome measures.

Outcomes	Measure	Time points
Primary Outcomes	Recruitment Feasibility	At 2 years
	Intervention adherence	At 4 weeks
	Retention Rate	At 24 weeks
	Adverse events and serious adverse events recorded	At 2, 4, 8, 16 and 24 weeks
	CDRS-R	Response at the end of treatment (Week 4) (defined as≥50% reduction in CDRS-R from baseline) or Remission at the end of treatment (Week 4) (defined as CDRS-R ≤ 28)
Secondary Outcomes	BDI-II	At 2, 4, 8, 16 and 24 weeks
	HAMA	At 2, 4, 8, 16 and 24 weeks
	SCARED	At 2, 4, 8, 16 and 24 weeks
	C-SSRS	At 2, 4, 8, 16 and 24 weeks
	PSQI	At 2, 4, 8, 16 and 24 weeks
	PedsQL 4.0	At 2, 4, 8, 16 and 24 weeks
	CGI-I	At 2, 4, 8, 16 and 24 weeks
	CGI-S	At 2, 4, 8, 16 and 24 weeks
	RRS	At 2, 4, 8, 16 and 24 weeks
Exploratory Outcomes	MRI	At 4, 8, 16 and 24 weeks
	THINC-It	At 4, 8, 16 and 24 weeks
	EEG	At 4, 8, 16 and 24 weeks
	fNIRS	At 4, 8, 16 and 24 weeks
	Eye tracking	At 4, 8, 16 and 24 weeks
	Facial expressions	At 4, 8, 16 and 24 weeks
	Acoustic features	At 4, 8, 16 and 24 weeks

CDRS-R, Children’s Depression Rating Scale-Revised; HAMA, Hamilton Anxiety Rating Scale; BDI-II, Beck Depression Inventory-II; SCARED, Screen for Child Anxiety Related Emotional Disorders; C-SSRS, Columbia-Suicide Severity Rating Scale; CGI-I, Clinical Global Impression-Improvement Scale; CGI-S, Clinical Global Impression-Severity Scale; RRS, Rumination on Responses Scale.

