### Safety considerations and adverse events

Internationally accepted definitions of adverse events (AEs) and serious adverse events (SAEs) will be applied. An AE will be defined as any unfavorable and unintended medical occurrence in a participant receiving transcranial magnetic stimulation, regardless of whether it is considered related to the intervention. An SAE will be defined as any event that results in death, is life-threatening, requires hospitalization or prolongation of hospitalization, results in persistent or significant disability or incapacity, or involves a congenital anomaly or birth defect. After each treatment session, participants will be systematically asked about any adverse reactions or other medical events experienced, and all AEs and SAEs will be documented and managed in accordance with the trial’s safety procedures.

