### Statistical analyses

#### Analysis populations and general principles.

All randomized participants who receive at least one treatment session will be included in the primary analysis set. Safety analyses will include all participants who receive at least one session of active or sham stimulation. Baseline characteristics will be summarized descriptively by treatment group. Continuous variables will be presented as mean and standard deviation or median and interquartile range, as appropriate, and categorical variables will be presented as frequencies and percentages.

As this is a pilot trial, the statistical analyses will focus primarily on estimation rather than definitive hypothesis testing. Effect estimates and corresponding 95% confidence intervals will be reported where appropriate, and P values will be interpreted cautiously as supportive rather than confirmatory. No formal adjustment for multiplicity is planned, given the exploratory nature of the trial.

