#### Analysis of primary outcomes.

Primary outcomes will be analyzed descriptively in accordance with the pilot nature of the trial. Feasibility outcomes will include recruitment feasibility, intervention adherence, and retention at the 6-month follow-up. Recruitment feasibility will be summarized as the number of participants enrolled during the recruitment period. Intervention adherence and retention will be summarized as frequencies and proportions, with corresponding 95% confidence intervals calculated where appropriate.

Safety outcomes will be analyzed in the safety analysis set, defined as all participants who receive at least one session of active or sham stimulation. The incidence of adverse events and serious adverse events will be summarized by treatment group as the number and proportion of participants experiencing at least one event. Event counts, severity, outcomes, and relationship to the intervention will also be summarized descriptively.

Preliminary clinical efficacy will be evaluated in terms of response and remission based on CDRS-R total scores. Response and remission rates will be summarized descriptively by treatment group at the end of treatment and at each follow-up assessment, with 95% confidence intervals. Exploratory between-group comparisons may be conducted using logistic regression models at individual post-baseline time points or generalized estimating equations for repeated binary outcomes across follow-up, as appropriate. Effect estimates will be presented as odds ratios with 95% confidence intervals.

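### One trigger list covers both stopping stimulation and leaving the study, so the plan permits ending follow-up for participants who have not withdrawn consent

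*Protocol article*

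**What the plan says.** The section 'Discontinuation of the intervention' has two paragraphs. The first deals with participants who choose to leave, and says that "no further study procedures or data collection will be performed after withdrawal". The second opens "Participants will discontinue the intervention or be withdrawn from the study under any of the following circumstances" and lists four triggers: (1) the participant asks to stop treatment or to leave the study; (2) a serious adverse event that the investigators or clinician judge to warrant discontinuation; (3) a clinician's decision to change the treatment plan because the participant's condition has changed; (4) unwillingness or inability to comply with the treatment or with study procedures.

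Under 'Primary outcomes', "CDRS-R total score will be assessed at baseline, at the end of treatment (week 4), and at follow-up weeks 8, 16, and 24". Table 1 (in 'Exploratory outcomes') lists "Adverse events and serious adverse events recorded" at weeks 2, 4, 8, 16 and 24, and the C-SSRS at the same weeks. Under 'Safety considerations and adverse events', "After each treatment session, participants will be systematically asked about any adverse reactions or other medical events experienced", and the definition of a serious adverse event includes one that "requires hospitalization or prolongation of hospitalization".

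Under 'Analysis populations and general principles', "All randomized participants who receive at least one treatment session will be included in the primary analysis set". Retention is the share of enrolled participants who complete the 6-month assessment.

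**The concern.** Stopping a treatment and leaving a trial are different events. The first is a clinical decision, after which the outcome can still be measured. The second ends measurement. Here one list serves both, joined by 'or', and the choice is left open for each participant.

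Three of the triggers can be met by someone who would willingly keep attending. They can also be related to outcome or harm: trigger (3) is a change in condition by its own terms, and an admission for worsening depression or suicidality is a serious adverse event that may be judged to meet trigger (2). If such participants are removed, the data lost concern response and remission, safety and retention, all of which are primary outcomes. An analysis plan can choose how to treat missing values, but it cannot recover visits that never took place. Recording the reason for discontinuation does not supply the outcome either.

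**Working it through.** The plan gives no figure to reproduce here. The sample size is pragmatic (15 × 3 = 45), and no dropout rate is stated. The check is a reading of the text, then a count from the schedule.

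**1. Which triggers need a withdrawal of consent?** Only (1), and only where the request is to leave the study. Triggers (2) and (3) rest on staff judgement. Trigger (4) overlaps with consent where the participant refuses study procedures, but inability to comply with treatment does not.

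**2. Does the text keep off-treatment participants in follow-up?** No section says so. The bar on data collection stands in the paragraph on the participant's own withdrawal, but it is worded for withdrawal in general, and no separate rule is given for withdrawal by staff.

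**3. What does removal lose?** From 'Primary outcomes' and Table 1:
- CDRS-R, post-baseline weeks 4, 8, 16, 24: removal before week 4 loses 4 of 4.
- C-SSRS and scheduled adverse-event time points, weeks 2, 4, 8, 16, 24: removal before week 2 loses 5 of 5; removal in week 3 loses 4 of 5.
- Systematic questioning about adverse events follows each session, so it stops with stimulation. After that, capture depends on the scheduled visits, which removal would end.
- BDI-II, HAMA, CGI-S and CGI-I are scheduled at week 2, so someone removed in week 3 can have some post-baseline scores.

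**4. What follows in the analysis?** After one session the participant is in the primary analysis set but has no response or remission status at any time point. The planned comparisons ("logistic regression models at individual post-baseline time points or generalized estimating equations for repeated binary outcomes across follow-up") then have no outcome row for that participant.

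**5. How much is left undetermined?** With n = 15 per arm and k participants of unknown status, an arm's response rate can lie anywhere in a range of width k/15. The difference between two arms with k lost in each has a range of width 2k/15. The values of k are assumed.

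| k per arm | One arm (k/15) | Two-arm difference (2k/15) |
|---|---|---|
| 1 | 6.7 points | 13.3 points |
| 2 | 13.3 points | 26.7 points |
| 3 | 20.0 points | 40.0 points |

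Illustration with assumed counts: k = 2 in each arm, 6 responders of 13 assessed on active treatment and 3 of 13 on sham.
- Active: 6/15 = 40.0% to 8/15 = 53.3%.
- Sham: 3/15 = 20.0% to 5/15 = 33.3%.
- Difference: (6 − 5)/15 = 6.7 to (8 − 3)/15 = 33.3 points. Among those assessed it is 46.2% − 23.1% = 23.1 points.

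For scale, the Wilson 95% interval for 6/15 is 19.8% to 64.3%, about 44 points wide. Sampling error is larger than these ranges, which come on top of it.

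**6. Retention.** Each removal by staff counts as a loss: 1/15 = 6.7 points in an arm, or 1/45 = 2.2 points overall.

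**The case against.** The strongest reply is that the section can be read benignly. Its heading concerns the intervention only, and trigger (1) itself distinguishes stopping treatment from leaving the study. Adherence and retention are defined separately, treatment discontinuation is summarised as a tolerability indicator, and adverse events are to be recorded through follow-up. 'Concomitant medication management' allows medication changes on clinical grounds within the trial, so a change of treatment need not end participation. The article is also a condensed text, and the full protocol may link each trigger to its consequence.

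Much of this stands, and it rules out several stronger readings:
- A reader might infer that the plan orders removal under these triggers. It does not; 'or' permits either course.
- A reader might infer that the data-collection bar plainly covers removal by staff. Its position suggests the participant's own withdrawal, where it is proper. The weakness is that it is not limited to that case.
- A reader might take every admission for worsening depression as a trigger. Trigger (2) covers only events judged to warrant discontinuation.
- A reader might conclude that imputation would have nothing to work with. Week-2 scales could inform it for someone removed in week 3. Only removal before week 2 leaves no post-baseline scale at all.
- A reader might take the ranges above as the bias this wording causes. They apply to any missing outcome at n = 15, and only removals of participants willing to stay are attributable to this section.

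The reply does not remove the point. The article states a conduct rule that allows removal without withdrawal of consent, and gives staff no basis for choosing between the two consequences. That is more than a detail left out. The separate outcome definitions show that the two states are recognised, but they do not say that follow-up continues in the first.

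**Conclusion.** The point holds as a weakness in a stated rule and should be fixed. The plan permits, but does not require, removal from follow-up of participants who have not withdrawn consent. Where this happens before week 4, no post-baseline CDRS-R exists, scheduled adverse-event and C-SSRS capture ends, and retention falls for a reason that is not the participant's choice.

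The size per event is 6.7 points of an arm's response rate left undetermined. The number of events is unknown, so the total effect cannot be stated, nor can the direction of any bias. The conclusion rests on the article's wording; if the full protocol already separates the two consequences, the article need only be brought into line. The trial is an estimation-focused pilot, which limits the seriousness, but the affected outcomes are all primary.

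**What to change.** Amend 'Discontinuation of the intervention' as follows:
- Triggers (2) and (3), non-compliance with treatment under (4), and a request only to stop treatment end stimulation and nothing else.
- These participants continue the scheduled assessments at weeks 4, 8, 16 and 24 (and week 2 if not yet reached), with adverse-event follow-up.
- Study withdrawal, and the bar on further data collection, apply only when consent or assent for follow-up is withdrawn.
- A participant who cannot or will not complete an assessment is recorded as missing that visit, and is still offered later visits and safety contact where they agree.

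The cost is a short amendment with ethics approval, revised consent wording, and some off-treatment visits at time points already in the schedule. The article places the end of recruitment in December 2026 and of data collection in June 2027, and provides an amendment route under 'Ethical considerations'.

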## Outcomes

### Primary outcomes

The primary outcomes of this pilot trial are feasibility, safety, and preliminary clinical efficacy.

Feasibility will be evaluated using three indicators: recruitment feasibility, intervention adherence, and retention at the 6-month follow-up. Recruitment feasibility will be defined as the number of participants successfully enrolled during the 2-year recruitment period. Intervention adherence will be defined as the proportion of participants who complete all 20 planned treatment sessions. Retention will be defined as the proportion of enrolled participants who complete the 6-month follow-up assessment.

Safety will be evaluated by recording the incidence of adverse events and serious adverse events throughout the treatment and follow-up periods. The type, severity, outcome, and relationship of each adverse event to the intervention will be documented.

Preliminary clinical efficacy will be evaluated using the CDRS-R. CDRS-R total score will be assessed at baseline, at the end of treatment (week 4), and at follow-up weeks 8, 16, and 24. Response will be defined as a reduction of at least 50% in the CDRS-R total score from baseline, and remission will be defined as a CDRS-R total score of 28 or lower [28]. Response and remission will be determined at post-baseline assessments, using the baseline CDRS-R total score as the reference.

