## Methods

### Study design and setting

This investigator-initiated, single-center pilot trial is designed to evaluate the feasibility, safety and preliminary clinical efficacy of rs-fcMRI-guided rTMS in adolescents with MDD. Participants will be randomly assigned to one of three parallel arms: conventional left dorsolateral prefrontal cortex (DLPFC)-targeted rTMS, rs-fcMRI-guided rTMS targeting an individualized DLPFC site defined by DLPFC-sgACC functional connectivity, or sham rTMS.

The study adopts a randomized, double-blind, three-arm, sham-controlled, parallel-group pilot design and will be conducted at the First Affiliated Hospital of Chongqing Medical University (Chongqing, China) from September 2025 to September 2027. A total of 45 adolescents will be enrolled, with 15 participants allocated to each group in a 1:1:1 ratio. Participant recruitment commenced in September 2025 and is expected to be completed by December 2026. Recruitment will be monitored throughout the study to assess enrolment feasibility and ensure timely participant accrual. At the time of manuscript submission, the study is ongoing, and no study results have been generated. Data collection is expected to be completed by June 2027, and study results are anticipated to be available by September 2027.

The study protocol was approved by the Ethics Committee of the First Affiliated Hospital of Chongqing Medical University (Ethical Approval No. 2025-533-01) and registered at ClinicalTrials.gov (NCT07185438).

This pilot trial consists of a 7-day screening period, a 4-week intervention phase, and follow-up assessments up to 6 months. After eligibility has been confirmed, participants and their legal guardians will provide written informed consent, and participants will undergo baseline assessments, including MRI. Participants will then be randomly assigned to one of three groups to receive a 4-week course of active or sham rTMS. Follow-up assessments will be performed at weeks 8, 16, and 24 to evaluate clinical outcomes and safety over time. Cognitive and multimodal measures, including EEG, fNIRS, eye-tracking measures, facial expression features, and acoustic features, will also be collected at baseline, at the end of treatment, and during follow-up as exploratory measures.

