In addition, study flow will be documented by recording the numbers of participants who are screened, excluded, randomized, treated, lost to follow-up, or withdrawn, together with reasons for non-participation, exclusion, or discontinuation. The schedule of enrolment, intervention, and assessments is presented in Fig 1 (SPIRIT schedule), and the overall study flow is shown in Fig 2 (Study flow chart).

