### Sample size

As a pilot trial, this study is not designed or powered to test definitive treatment efficacy. A total of 45 MDD adolescents will be enrolled, with 15 participants allocated to each of the three study arms. The sample size was determined pragmatically on the basis of feasibility, anticipated clinical capacity, and available study resources. This sample size is intended to provide estimates of recruitment feasibility, intervention adherence, retention, safety, and preliminary clinical efficacy signals, as well as variability parameters needed to refine the protocol and inform the sample size calculation for a future fully powered randomized controlled trial.

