## Ethics and dissemination

### Ethical considerations

This investigator-initiated study at the First Affiliated Hospital of Chongqing Medical University is a randomized, double-blind, three-arm, sham-controlled, parallel-group pilot clinical trial. All study procedures will be conducted in accordance with the ethical standards of the relevant national and institutional committees on human experimentation and with the Declaration of Helsinki (1975), as revised in 2013. The study protocol was approved by the Ethics Committee of the First Affiliated Hospital of Chongqing Medical University on 21 August 2025 (Ethical Approval No. 2025-533-01), and the trial was registered at ClinicalTrials.gov on 15 September 2025 (Registration No. NCT07185438). The trial protocol and statistical analysis plan are publicly available through the trial registration record. Participant recruitment commenced on 1 September 2025 and is expected to be completed on 31 December 2026. Any protocol modifications, including changes to study procedures or participant safety measures, will be documented as protocol amendments and communicated in a timely manner to the Ethics Committee and relevant investigators. All amendments will be reviewed and approved by the Ethics Committee before implementation to ensure ongoing compliance with ethical standards.

Written informed consent will be obtained before enrolment. Because all participants are adolescents, the principal investigator will ensure that written informed consent is obtained from participants’ legal guardians and that assent or consent from participants is obtained in accordance with applicable ethical and legal requirements. Before consent is obtained, participants and their guardians will receive a clear explanation of the study procedures, potential risks, and anticipated benefits, and they will have the opportunity to ask questions.

Participants will be reimbursed for study-related examination costs incurred during the trial, and all required study equipment will be provided at no cost. Upon completion of study participation, participants will receive compensation for transportation expenses related to trial visits. In the event of any trial-related adverse events, necessary medical expenses will be covered and additional compensation will be provided in accordance with institutional policies and applicable regulations.

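### The primary outcome of recruitment feasibility is counted over two years, but the stated recruitment dates span 16 months

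*Protocol article*

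**What the plan says.** The article gives the length of recruitment in several places.

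- **Primary outcomes:** "Recruitment feasibility will be defined as the number of participants successfully enrolled during the 2-year recruitment period". Table 1 repeats the two-year time point for this outcome.
- **Ethical considerations:** "Participant recruitment commenced on 1 September 2025 and is expected to be completed on 31 December 2026".
- **Study design and setting** agrees by month: "Participant recruitment commenced in September 2025 and is expected to be completed by December 2026". It places the whole study "from September 2025 to September 2027" and adds: "Data collection is expected to be completed by June 2027, and study results are anticipated to be available by September 2027". On follow-up it says: "Follow-up assessments will be performed at weeks 8, 16, and 24 to evaluate clinical outcomes and safety over time".
- **Sample size** fixes the total: "A total of 45 MDD adolescents will be enrolled, with 15 participants allocated to each of the three study arms".
- **Analysis of primary outcomes** summarises recruitment feasibility as a number enrolled over the recruitment period, without giving that period a length.
- Separately, **Study design and setting** says the study flow will record the "numbers of participants who are screened, excluded, randomized, treated, lost to follow-up, or withdrawn", with reasons. The article does not link these data to the recruitment outcome.

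**The concern.** Recruitment feasibility is the first feasibility indicator listed among the primary outcomes. The Discussion says the feasibility results will help decide whether the protocol needs changing before a larger trial. The definition's window does not match the recruitment dates stated twice elsewhere, and the analysis section does not settle which applies.

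The window decides two things: the date on which the outcome is read, and whether participants enrolled after the planned close count towards it. With a two-year window, a trial that missed its December 2026 close and filled slowly during 2027 could report the same number as one that filled on time.

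The measure has a related weakness. It is a count with a planned stopping point, so once 45 is reached it does not separate quick from slow recruitment, or a high screening yield from a low one.

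**Working it through.** **Inputs.** Recruitment dates: Ethical considerations, and by month Study design and setting. Follow-up of 24 weeks (168 days), end of data collection (June 2027) and results (September 2027): Study design and setting. Two-year window: Primary outcomes and Table 1. Total of 45: Sample size.

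**Step 1. Length of the stated recruitment period.**
1 September 2025 to 31 December 2026, both days included: 122 days in 2025 + 365 days in 2026 = 487 days. 487 / 30.4375 = 16.0 months. The two-year figure is not reproduced from these dates. It does match the whole study period, September 2025 to September 2027.

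**Step 2. Which window fits the rest of the calendar?**

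| Recruitment window | Last enrolment | Plus 168 days | By June 2027? | By September 2027? |
|---|---|---|---|---|
| 16 months | 31 Dec 2026 | 17 Jun 2027 | yes | yes |
| 2 years | 31 Aug 2027 | 15 Feb 2028 | no | no |

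Adding the 7-day screening period to the first row gives 24 June 2027, which still fits. Working backwards, the latest enrolment that allows a week-24 visit by 30 June 2027 is 13 January 2027, about 16.4 months after opening. The latest that allows one by 30 September 2027 is 15 April 2027, about 19.4 months. Neither reaches 24 months.

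**Step 3. How far apart are the two windows?**
From 31 December 2026 to 31 August 2027 is eight months. The pace needed for 45 is:
- over 16 months: 45 / 16 = 2.81 per month
- over 24 months: 45 / 24 = 1.875 per month

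At the slower pace, enrolment by 31 December 2026 would be 1.875 × 16 = 30. If recruitment then continued, a count at two years could still be 45.

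**Step 4. When does the choice matter?** As an illustration, assume Poisson accrual at a constant rate. The article states neither. The probability of reaching 45 is then:

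| True rate per month | Within 16 months | Within 24 months |
|---|---|---|
| 1.875 | 0.6% | 52% |
| 2.5 | 23% | 98% |
| 3.5 | 94% | about 100% |
| 5 | about 100% | about 100% |

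The windows differ sharply at slow or moderate rates. At fast rates both give 45, and the count no longer distinguishes one rate from another.

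**Step 5. Screening yield.** The article gives no expected number screened. Assuming 60 to 225 screened, the same count of 45 would correspond to a yield from 45 / 60 = 75% down to 45 / 225 = 20%.

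**The case against.** The strongest reply is that this is a slip of labelling: the study's duration was written where the recruitment period belongs. The outcome is a count, so if recruitment closes in December 2026 as planned, the number at two years equals the number at 16 months. The analysis section does not repeat the two-year figure. All this is fair, and it limits the consequence to an overrun. It does not remove the conflict, because the article states both periods and a late close is exactly what a recruitment outcome should reveal.

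Three stronger readings are tempting, and the article does not support them.

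- **That the outcome cannot measure feasibility.** A count below 45 at a fixed date shows a shortfall directly. The study flow data are already planned, and recruitment is to be monitored throughout.
- **That the accrual rate passed to the next trial will be a third too low.** 1.875 is two thirds of 2.81, but nowhere does the article divide by 24 months, and the actual opening and closing dates will be known.
- **That the outcome could be declared met despite a delay.** The article sets no success criterion, so there is nothing to declare met. A target may stand in the full protocol or the analysis plan, and its absence from a condensed article is not counted here.

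The ceiling of 45 is also an inference from the fixed total; the article does not describe a cap. Rates and yields may likewise be specified in the fuller documents, so adding them is an improvement rather than the correction of an error.

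**Conclusion.** The definition is wrong as written. A primary outcome uses a 24-month recruitment window where the stated dates give 16 months, and only 16 months is compatible with 24 weeks of follow-up and data collection ending in June 2027. The gap is eight months in the date of reading and in who may be counted. It changes the reported number only if recruitment runs past 31 December 2026. In that event the two-year wording would include late recruits and would not show the delay.

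The second part is weaker: the bare count carries little information on speed or yield once the planned 45 is reached. This assumes that enrolment stops at 45.

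No treatment comparison is affected. The point still merits correction because it lies in the definition of a primary outcome and costs little to put right.

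**What to change.** 1. In Primary outcomes and Table 1, replace the two-year period with the stated recruitment dates, 1 September 2025 to 31 December 2026. If those dates are themselves out of date, correct them, and the data-collection and results dates with them. Check the registered outcome for the same two-year wording.
2. Keep the number enrolled by 31 December 2026 as the outcome. Retain the term enrolled, or say explicitly if randomised is meant, since consent and baseline assessment come before randomisation.
3. Report beside it, as descriptive summaries:
   - the number enrolled per month of actual open recruitment, with a 95% confidence interval
   - enrolled/screened and enrolled/eligible, each with a 95% confidence interval, taken from the study flow data, with eligible counted as those screened less those excluded on the eligibility criteria.

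**Cost.** No new procedures or data are needed: the dates and flow counts are already to be recorded. The change is a minor amendment, which under Ethical considerations needs Ethics Committee approval before implementation, and possibly a registry update. It alters the wording of a primary outcome while recruitment is under way on the stated schedule, so the reason should be recorded with the amendment.
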